# Uptake of Task-Strengthening Strategy for Hypertension (TASSH) control within Community-Based Health Planning Services in Ghana: study protocol for a cluster randomized controlled trial

**DOI:** 10.1186/s13063-020-04667-7

**Published:** 2020-10-02

**Keywords:** Task strengthening, Hypertension control, Practice facilitation, Implementation science, Community-Based Health Planning Services, Ghana, Sub-Saharan Africa

## Abstract

**Background:**

Physician shortage is a major barrier to hypertension (HTN) control in Ghana, with only one physician to 10,000 patients in 2015, thus limiting its capacity for HTN control at the primary care level such as the Community Health Planning and Services (CHPS) compounds, where most Ghanaians receive care. A Task-Shifting Strategy for HTN control (TASSH) based on the WHO Cardiovascular (CV) Risk Package is an evidence-based strategy for mitigating provider- and systems-level barriers to optimal HTN control. Despite its effectiveness, TASSH *remains untested* in CHPS zones. Additionally, primary care practices in low- and middle-income countries (LMICs) lack resources and expertise needed to coordinate multilevel system changes without assistance. The proposed study will evaluate the effectiveness of practice facilitation (PF) as a quality improvement strategy for implementing TASSH within CHPS zones in Ghana.

**Methods:**

Guided by the Consolidated Framework for Implementation Research and the Reach, Effectiveness, Adoption, Implementation, and Maintenance framework, we will evaluate, in a hybrid clinical effectiveness-implementation design, the effect of PF on the uptake of an evidence-based TASSH, among 700 adults who present to 70 CHPS zones with uncontrolled HTN. Components of the PF strategy include (a) an advisory board that provides leadership support for implementing the intervention within the CHPS zones and (b) trained task-strengthening facilitators (TSFs) who serve as practice coaches to provide training, and performance feedback to community health officers (CHOs) who will deliver TASSH at the CHPS zones. For this purpose, the TSFs are trained to identify, counsel, and refer adults with uncontrolled HTN to community health centers in Bono East Region of Ghana.

**Discussion:**

Uptake of community-based evidence-supported interventions for hypertension control in Ghana is urgently needed to address the CVD epidemic and its associated morbidity, mortality, and societal costs. Findings from this study will provide policymakers and other stakeholders the “how to do it” empirical literature on the uptake of evidence-based task-strengthening interventions for HTN control in Ghana and will serve as a model for similar action in other low, middle-income countries.

**Trial registration:**

ClinicalTrials.gov, NCT03490695. Registered on 6 April 2018.

**Protocol version and date:**

Version 1, date: 21 August, 2019.

## Background

Shortage of healthcare workers is a major barrier to hypertension (HTN) control in Ghana, where in 2017 the density of doctors, nurses, and midwives was 2.65 per 1000 population [1, 2]. This acute shortage of physicians limits Ghana’s capacity to control HTN in adults at the basic primary care level such as the Community-Based Health Planning and Services (CHPS) zones, where majority of Ghanaians receive their care [3]. The shortage of health workers is partly due to brain drain of health workers to high-income countries for better standard of living, higher salaries, and stable political conditions [1, 4, 5]. There is thus an urgent need for strategies that help reduce the burden of NCDs in Ghana, particularly community-based strategies targeted at the rational use of available resources [6, 7]. One such approach is a task-shifting strategy, defined as the rational distribution of primary care duties from physicians to non-physician healthcare providers [8–12].

Task shifting is useful in low-resource settings, such as SSA countries, who face acute healthcare human resource crisis [8–12]. In order to maximize the efficient use of resources, healthcare tasks are shifted from higher-trained health workers to less-trained health workers [8, 9]. In this context, shifting the tasks of CV risk assessment and management of uncomplicated CV risk factors, such as HTN from physicians to non-physician healthcare providers (NPHCPs) such as community health workers and nurses, is a viable and cost-effective strategy. Growing evidence suggests that patients with HTN can be cared for by NPHCPs, who provide adequate counseling of healthy lifestyle to patients almost as often as physicians [8, 13].

We recently demonstrated, in a cluster randomized control trial in 32 district hospitals and community health centers in Ghana, that an evidence-based Task-Shifting Strategy for HTN control (TASSH) based on the WHO Cardiovascular Risk Package, delivered by community health nurses (CHNs), led to 1.34 times greater systolic blood pressure reduction than provision of health insurance [13]. Although TASSH led to a significant reduction in systolic BP, its widespread implementation and dissemination within the Ghana’s Community-Based Health Planning and Services (CHPS) zones have not been evaluated. CHPS zones are unique settings for implementation of TASSH because of their use of community health officers (CHOs) who deliver primary care services [3]. At the hub of this primary care system is the widespread implementation of the CHPS program, which represent the “ground level” of Ghana’s health system, and provide basic primary care services to people in their communities, through community engagement in the planning and delivery of services [3]. CHPS utilizes CHOs living in a defined community to offer limited curative and preventive healthcare services to the population [3]. The use of CHPS as a platform for healthcare delivery in every community in Ghana [3] allows us to evaluate the adoption and maintenance of TASSH in community settings.

This study provides a unique opportunity for us to fill this research-to-practice gap by evaluating the effectiveness of a practical and replicable strategy for implementing TASSH among adults who present to CHPS zones with uncontrolled HTN*.* Systematic reviews show that effective implementation strategies of evidence-based interventions are typically multilevel, and are tailored to the practice context [14, 15]. However, primary care practices in low- and middle-income countries (LMICs) lack resources and expertise needed to coordinate multilevel system changes without assistance [16]. One implementation strategy that may effectively overcome this barrier is practice facilitation (PF) via provision of external expertise on practice redesign, and a tailored approach to implementing guideline-concordant care [16, 17]. Although PF is well studied in high-income countries [18–20], its role remains untested in LMICs.

### Objectives

The study has four specific objectives:
*Aim 1*: Identify practice capacity for the adoption of TASSH in CHPS zones and develop a culturally tailored PF strategy using qualitative methods.*Aim 2a*: Evaluate in a cluster randomized controlled trial (RCT) the effect of PF versus usual care (UC) on the adoption of TASSH across 70 CHPS zones at 12 months post-randomization.*Aim 2b*: Compare in a cluster RCT design the clinical effect of PF versus UC on systolic blood pressure (BP) reduction among 700 adults with uncontrolled HTN at 12 months post-randomization.*Aim 3*: Evaluate the sustainability of TASSH implementation across the CHPS zones at 24 months post-randomization (1 year after completion of the trial).*Aim 4*: Evaluate the mediators of the adoption of TASSH across the CHPS zones at 12 months post-randomization.

## Methods

### Trial design

Using a hybrid clinical effectiveness-implementation design [21], we will conduct this study in 3 sequential phases: (1) The first is a pre-implementation phase, based on the Consolidated Framework for Implementation Research (CFIR) [22] to assess inner setting variables and provider characteristics likely to influence the adoption of TASSH within the CHPS zones. This information is used to develop and user-test a culturally tailored PF strategy to implement TASSH. (2) Next is an implementation phase, which evaluates in a cluster RCT the effect of the PF strategy versus usual care on the adoption of TASSH as well as clinical effectiveness on systolic BP reduction at 12 months post-randomization across the CHPS zones. We will also evaluate the mediators of the adoption of TASSH in the CHPS compounds. (3) Another is a post-implementation phase which evaluates the sustainability of TASSH implementation across participating CHPS zones at 24 months (1 year after completion of the trial). Measures for the implementation and the post-implementation phases are guided by CFIR and the RE-AIM framework [22–25].

### Study setting and participant characteristics

The study is currently ongoing in 70 of the 97 CHPS zones in three contiguous districts within the Bono East Region (Kintampo North, Kintampo South District, and Nkoranza North District) of Ghana. The study area is predominantly rural and mostly farming communities [26, 27]. About 40% of the adult population have no education. Access to healthcare is mainly at the community-level healthcare which is limited. About 50% of the population have valid health insurance cards that enable them to access basic healthcare under the National Health Insurance Scheme. In 2016, 2555 community members aged ≥ 18 years (mean age of 43 years, SD 17; 60.5% female) participated in a cross-sectional health survey, which documents the prevalence of hypertension as 28.1% (95% CI 26.3–29.8), with pre-hypertension prevalence of 42.5% [28]. Approximately 45.9% (95% CI 42.2–49.6) of hypertensive respondents were aware of their diagnosis; of those aware, 41.3 (95% CI 36.1–46.8) sought medical treatment and had their hypertension controlled, while 58.7% (95% CI 53.2–63.9) did not seek any medical treatment. Tobacco use in the area is about 3%, and the prevalence rate of obesity among the adult population (> 40 years) is 11% [28].

### Sites and participant recruitment

Participants will be recruited from eligible CHPS zones that (1) have at least 2 community health workers (CHWs) employed in the CHPS program and (2) are certified as a National Health Insurance Scheme provider. A total of 70 CHPS zones will be recruited into this trial.

Patients for the study are identified from the CHPS zones by the CHWs during provision of their routine services and visits with families or through of the conduct of health fairs in participating CHPS zones. Each zone is expected to recruit consent 10 consecutive patients who meet the eligibility criteria below. Study coordinators will obtain individual consent from eligible patients before they can be enrolled in the study. For patients recruited to the CHPS zones, once eligibility is confirmed, all patients regardless of their group assignment will have a total of four study visits: baseline, 6 months, 12 months, and 24 months post-randomization. The structure of each study visit and the respective measures will be the same for each group. A total 70 CHPS compounds and 700 patients will be enrolled in this study with approximately 10 patients per CHPS compound. Patients may withdraw from or refuse to participate in the trial at any point, and it will not affect the clinical care they receive.

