#### Patients

Adults who (a) are patients registered to receive care at CHPS zone, (b) are aged 40 years and older, (c) have average BP (140–179/90–100 mmHg) from two separate visits to the CHPS zone at least 1 week apart, and (d) have the ability to provide informed consent were included.

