### Randomization and blinding

Randomization will occur at the level of the CHPS zones. Each CHPS zone will be randomly assigned to one of the two arms: Group A will receive the practice facilitation strategy herein referred to as a task-strengthening facilitation (TSF) strategy for 12 months. Assessment of adoption ratings on TASSH will be made at 12 months post-randomization, and sustainability will be assessed at 24 months post-randomization. Group B will receive usual care practices (screen, counsel, and refer patients without practice facilitation) at CHPS zones [27]. Adoption ratings of TASSH will be assessed for group B at 12 months post-randomization, and sustainability assessment will occur at 24 months post-randomization. The sequence of randomization will be generated by study statistician and kept in sealed opaque envelopes away from the study sites in accordance with the CONSORT guidelines [29]. Sites will be informed of their randomization group by telephone and email.

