
##### Engagement of the community to create a community urgency and persistency of the importance of HTN screening and referral for adults

This component of the intervention will be conducted by the Local Steering Committee that comprises the leadership of the regional health directorate, public health nurses, director of surveillance, coordinator for the community engagement committee, data manager, and the regional NCD resource person. This committee is already convened as part of the Ghana Health Services and will coordinate the community engagement activities via health fairs, visits to health centers, and other events organized by the Regional Health Directorate of the Brong-Ahafo Region where the participating CHPS zones are located.

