## Trial status

The study-specific manual of operations and policies has been developed. The first cohort (18 CHPS zones) has been randomized and enrolled. Also, 72 CHOs from the 36 zones have been trained to start implementation. The Data Safety and Monitoring Board has been formed and has already had its first meeting which was held on 2 July 2019. Steering Committees have been constituted and already had 4 meetings. The pre-implementation activities and contextual assessment of aim 1 have been completed. Enrolment into the trial started in November 2019 and should be completed by July 2021. This is study protocol version 4.0, and the version date is August 21, 2019.

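### Nothing in the protocol keeps a zone's arm from the staff who find and consent its patients, so the secondary SBP comparison is at risk of recruitment bias of unknown size and direction

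*Protocol article*

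**What the plan says.** **Who finds the patients.** Under Sites and participant recruitment: "Patients for the study are identified from the CHPS zones by the CHWs during provision of their routine services and visits with families". Health fairs held in the trial's zones are named as a second route. The same section continues: "Each zone is expected to recruit consent 10 consecutive patients who meet the eligibility criteria below". On consent it says: "Study coordinators will obtain individual consent from eligible patients before they can be enrolled in the study".

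**Who knows the arm.** Randomization and blinding makes the zone the unit of randomisation and keeps the sequence in sealed opaque envelopes away from the sites. It then says: "Sites will be informed of their randomization group by telephone and email". Masking and blinding states that patients, CHOs and study coordinators cannot be blinded. The one bias it treats is the BP reading, through an automated device.

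**What facilitation changes.** Under Practice facilitation (group A), facilitators sort the CHOs' tasks into screening for hypertension, counselling and referral, and coach each. Under Study outcomes, the first of the three adoption metrics is the rate of newly detected hypertension. The Aim 2a analysis hypothesises higher adoption under PF.

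**Health fairs.** The community-engagement text, placed under group A and called an intervention component, says a steering committee "will coordinate the community engagement activities via health fairs" and other events.

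**Status.** Under Trial status: "The first cohort (18 CHPS zones) has been randomized and enrolled".

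**The concern.** Randomising zones balances the zones. It balances the patients only if they are chosen without regard to the arm. If staff who know the arm decide whom to screen and approach, or if the intervention changes how cases are found, the two groups can differ at entry: in the share newly detected versus already known, in how they came to notice, or in how their screening BP was taken. Each of these can affect the expected 12-month change in SBP, including regression to the mean.

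The protocol's own hypothesis makes this more than a generic worry. If PF works on its first adoption metric, detection of hypertension differs by arm, and detection is the step that supplies the Aim 2b patients. Intent-to-treat and maximum likelihood (Consideration of missing data) deal with loss after entry, not with selection into the sample. At stake is the trial's clinical-effectiveness result. The adoption primary is not the subject of this point.

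**Working it through.** **Order of steps, as far as the text goes**

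1. Zones are randomised and sites are told the result (Randomization and blinding). No time relative to patient identification is given.
2. Community health workers (CHWs) find patients and coordinators consent them (Sites and participant recruitment). The masking section speaks of CHOs. The zone criterion of at least two workers appears once with each term (Sites and participant recruitment; Inclusion criteria), so these appear to be the same staff.
3. No sentence holds disclosure back until a zone's patients are enrolled, and none provides a recruiter masked to the arm.

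**The plan's own sample size, reproduced first**

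Inputs from Sample size and power estimates: d = .50, alpha .05, power .80, ICC .10, 2 CHOs per compound. The two-tailed test is from the Aim 2a analysis.

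- Unclustered: 2 × (1.960 + 0.842)² / 0.50² = 62.8, so 63 CHOs per arm.
- Design effect: 1 + (2 − 1) × .10 = 1.10.
- 63 × 1.10 = 69.3 CHOs per arm; 2 × 69.3 / 2 = 69.3 compounds in total, against 70 stated. This agrees.

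**Precision of the SBP comparison**

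- Patients per arm: 35 × 10 = 350.
- Design effect at ICC .10: 1 + (10 − 1) × .10 = 1.90.
- Effective number per arm: 350 / 1.90 = 184.2.
- Standard error: √(2 / 184.2) = 0.104 SD of change.
- Power at d = .50: 0.997 (t test, 68 df). This fits the plan's statement that SBP power is well above .80.

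**Effect of a recruitment shift when PF has no true effect on SBP**

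The size of the shift b is an assumption; the document gives none. Noncentrality is b / 0.104. Rejection is the two-sided 5% t test with 70 − 2 = 68 df.

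| Assumed shift b (SD of change) | b / SE | Rejection, ICC .10 | Rejection, ICC .05 (assumption) |
|---|---|---|---|
| 0.05 | 0.48 | 7.6% | 8.4% |
| 0.10 | 0.96 | 15.7% | 19.2% |
| 0.15 | 1.44 | 29.5% | 36.9% |
| 0.20 | 1.92 | 47.3% | 58.2% |

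At ICC .05 the design effect is 1.45, the effective number per arm 241.4 and the standard error 0.091.

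The document gives no SD of SBP change. For SDs of 10 to 20 mmHg (assumption), shifts of 0.05 to 0.20 SD span 0.05 × 10 = 0.5 mmHg to 0.20 × 20 = 4 mmHg. The high power for SBP gives no protection: a small standard error makes a small bias more likely to be declared significant.

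**The case against.** **The order is not stated.** No sentence says that patients are found after disclosure. Being unable to blind staff to the intervention is not the same as the arm being known at recruitment. The Trial status sentence has zones as its subject and fixes no order for patients. The flow chart and SPIRIT figure, where the order might appear, are not shown. This stands. A reader might infer that recruiters do know the arm when they pick patients; the document leaves that open and does not establish it.

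**Both arms are trained.** Group B CHOs also learn the 5 A's and referral, and facilitation is said to be the only difference. Trial status reports 72 CHOs from 36 zones trained while 18 zones were randomised, which suggests training is not tied to allocation. The masking section schedules facilitation at months 3, 6 and 9. This narrows the likely difference in case-finding. It does not remove it, because facilitation also includes regular calls (given both as monthly and as weekly) that could act earlier, and knowledge of the arm alone can influence who is approached.

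**Fairs may run everywhere.** Recruitment fairs are described for participating zones generally. The numbered list of PF components does not include community engagement, and the committee already exists within the health service. A reader might infer that only group A zones hold fairs; the text does not say so. It also does not say that group B zones hold them.

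**Safeguards exist.** Patients are consecutive, must be registered at the zone, and qualify on BP "from two separate visits to the CHPS zone at least 1 week apart". Covariates showing baseline differences enter the model with their time interactions (Aim 2a; Aim 2b follows a similar strategy). These help. But the consecutive rule applies to people who already meet the criteria, not to whom staff screen. The BP criterion limits the BP range, not the route or the new/known mix. Covariate adjustment is conditional, reaches only what is measured, and names neither route nor new versus known diagnosis.

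**Conclusion.** The point holds as an unguarded risk, not as a demonstrated bias. As written, nothing prevents a zone's patients from being identified and consented by staff who know its arm, while PF is meant to change the case-finding that supplies those patients. The stated safeguards are partial.

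Size and direction cannot be derived. The roughly 8%, 16%, 29% and 47% rejection rates rest on the plan's ICC of .10 and 10 patients per compound, on assumed shifts of 0.05 to 0.20 SD, and on no true effect. They show how sensitive the test is, not what will happen. It would also go too far to conclude that the SBP comparison is already compromised, or to put a figure in mmHg on the bias.

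The outcome is secondary, but it carries the trial's clinical claim. The remedy is cheap and most zones can still benefit: Trial status reports a first cohort of 18 of the 70 zones, with enrolment running to July 2021. The change should be made.

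**What to change.** 1. **Zones not yet enrolled:** complete patient identification, consent and baseline measurement before the zone's arm is disclosed and before facilitation starts there. State this order in the protocol. If it is already followed, stating it is enough.
2. **Recruitment routes:** use the same routes in both arms, including any health fairs, and say whether the community-engagement fairs take place in group B zones.
3. **Zones enrolled after disclosure:** record recruitment route and new versus known diagnosis where available, and report an SBP sensitivity analysis adjusted for both. This supports the main analysis but cannot fully repair selection on unmeasured factors.

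**Cost:** a short delay in each remaining zone between its selection and the start of facilitation. The two-visit BP criterion already sets a minimum of one week. Items 1 and 2 mainly re-order or align existing steps and do not change the target of 700 patients. Item 3 adds two data items and one analysis.

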### Inclusion criteria

#### CHPS zones

Eligible CHPS zones must have at least 2 community health officers (CHOs) employed in the CHPS program and be a certified National Health Insurance Scheme provider.

#### Patients

Adults who (a) are patients registered to receive care at CHPS zone, (b) are aged 40 years and older, (c) have average BP (140–179/90–100 mmHg) from two separate visits to the CHPS zone at least 1 week apart, and (d) have the ability to provide informed consent were included.

